### Machine learning analysis

ML models will be trained to predict the risk of death for infants with signs of PSBI. The presence/absence of PSBI signs recorded over multiple visits, as well as available clinical and treatment data, will be used as input features. See supplemental table S1 (in online supplemental file 1) for a preliminary list of available predictors that are common to the ANISA and AFRINEST studies (which includes all predictors in AFRINEST) and supplemental table S2 (in online supplemental file 1) for a list of predictors available in the ANISA dataset. We will use two approaches. First, multivariate modelling will be applied to obtain precise contributions of each sign and combinations of signs to the mortality rate. In this approach, models will be built by applying standard ML models, specifically Elastic Net, XGBoost and Stabl.^33^,^35^ Presence/absence of PSBI signs at different times will be treated as separate features, and the model will predict the risk of death on a specific day given the signs on that day and in the previous 6 days.

Three models will be analysed, each specifying how the risk of death depends on PSBI signs with increasing levels of detail. We denote the predicted (dependent) variable as Y∈{0,1}

where

$$Y=\left\{ \begin{array}{l} 1,\;if\;infant\;dies\;in\;the\;7-day\;window\\ 0,\;otherwise \end{array}\right.$$

In our first (simplest) model 1, we will assume a standard logistic model for the probability of infant death given the signs in the previous 7 days.^36^ We include interaction terms between two different signs to quantify the effect of the presence of two signs on the probability of infant death. The probability that an infant dies given signs in the previous 7 days is then given by

$$\log\left(\frac{P\left(Y=1|X_{1},\ldots ,X_{p}\right)}{P\left(Y=0|X_{1},\ldots ,X_{p}\right)}\right)=\beta_{0}+\sum_{i=1}^{7}\beta_{i}X_{i}+\sum_{i=1}^{7}\sum_{j=2,\;j>i}^{7}\beta_{ij}X_{i}X_{j}+\sum_{i=8}^{p}\beta_{i}X_{i}$$

where input features $X_{i},i=1,\ldots ,7$are given by

$$X_{i}=\left\{ \begin{array}{l} 1,\;if\;sign\;i\;is\;present\;at\;any\;time\;during\;7\;days\\ 0,\;otherwise \end{array}\right.$$

and $X_{i},i=8,\ldots ,p$ are input features for each of the baseline covariates.

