The output of the ML model will provide adjusted ORs for the risk of death for each sign and the interaction of signs. ORs for each sign *i* will be obtained as: $OR_{i}=e^{\beta_{i}}$. A limitation of model 1 is that the risk of death depends only on the presence/absence of each of the signs at any time during the 7-day window but does not account for the time lag between the sign and the outcome. Consequently, the probability in model 1 will be the same for two infants that died on different days but had the same signs.

In our second model, we will capture the day in the 7-day window when the death occurred, as follows. For each infant indexed by b that died on day $k_{b}\in \left\{0,\ldots ,6\right\},$ we define $k_{b}$ outcomes $Y_{bk}\in \left\{0,1\right\},k=1,\ldots ,k_{b}$

where

$$\begin{array}{l} Y_{bk}=\left\{ \begin{array}{c} 1,if\;k=k_{b}\\ 0,k§lt;k_{b} \end{array}\right.k=1,\ldots ,\;k_{b}. \end{array}$$

For infants that survived, we have $Y_{bk}=0,\text{for}\;k=0,\ldots ,6$.

We then consider model 2, which, similar to model 1, is a logistic model:

$$\log\left(\frac{P\left(Y_{bk}=1|X_{1},\ldots ,X_{p}\right)}{P\left(Y_{bk}=0|X_{1},\ldots ,X_{p}\right)}\right)=\beta_{0}+\sum_{i=1}^{7}\beta_{i}X_{ik}+\sum_{i=1}^{7}\sum_{j=2,\;j>i}^{7}\beta_{ij}X_{ik}X_{jk}+\sum_{i=8}^{p}\beta_{i}X_{i}$$

where $X_{ik},i=1,\ldots ,7$ denotes the presence or absence of sign *i* at any time before or at day k:

$$X_{ik}=\left\{ \begin{array}{l} 1,\;if\;sign\;i\;is\;present\;at\;any\;day\;before\;day\;k\;or\;at\;day\;k\\ 0,\;otherwise \end{array}\right.$$

In our third model, we capture the timing of each clinical sign. To achieve this, we consider separate features for the presence/absence of PSBI signs for each day:

$$\log\left(\frac{P\left(Y_{k}=1|X_{1},\ldots ,X_{p}\right)}{P\left(Y_{k}=0|X_{1},\ldots ,X_{p}\right)}\right)=\beta_{0}+\beta_{1}^{0}X_{1}^{k}+\beta_{1}^{-1}X_{1}^{k-1}+\ldots +\beta_{1}^{-6}X_{1}^{k-6}+$$

$$\beta_{2}^{0}X_{b}^{k}+\ldots \beta_{b}^{-6}X_{b}^{k-6}+\ldots +\beta_{7}^{-6}X_{7}^{k-6}+\sum_{i=8}^{p}\beta_{i}X_{i}$$

where input features $X_{i}^{k},i=1,\ldots ,7,k=0,\ldots ,6$ are given by

$$X_{ik}=\left\{ \begin{array}{l} 1,\;if\;sign\;i\;is\;present\;at\;any\;day\;before\;day\;k\;or\;at\;day\;k\\ 0,\;otherwise \end{array}\right.$$

In the case of model 3, 1-hot encoding will be used to construct matrix X containing all input features.

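### Model 2 indexes deaths and survivors differently, so read literally a death on day 0 of the window has no record

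*Protocol article*

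**What the plan says.** In the Machine learning analysis section, the purpose of the second model is stated as "we will capture the day in the 7-day window when the death occurred". Its outcome is then defined in three steps.

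- The rule for deaths begins "For each infant indexed by b that died on day" k_b, with k_b in {0,…,6}. Day 0 is therefore an admissible day of death.
- For such an infant the plan defines k_b outcomes Y_bk, with k running from 1 to k_b. Y_bk is 1 when k = k_b and 0 when k < k_b. The range 1 to k_b is repeated in the displayed definition.
- For the other group it says "For infants that survived, we have" Y_bk = 0 with k running from 0 to 6, which is seven records.

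The sign feature X_ik counts a sign seen on day k or on any earlier day. The opening of the same section says "the model will predict the risk of death on a specific day given the signs on that day and in the previous 6 days". The linear predictor of model 2 has a single intercept and no term for day.

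**The concern.** The two groups are given different starting days. An infant who dies starts at day 1 and a survivor starts at day 0. Whether a day-0 record exists therefore depends on the outcome, and the deaths with k_b = 0 drop out.

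Model 1 codes Y = 1 for any death in the 7-day window. As written, models 1 and 2 would not rest on the same deaths, although they are presented as the same question in increasing detail. The section says that its results will be considered in possible changes to IMCI and perhaps in an app for community health workers. Understated risk would be an unhelpful direction of error for either use.

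**Working it through.** **Step 1: records implied by the written ranges.** The inputs are the three index rules above.

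| Infant | Records as written | Records with k = 0,…,k_b |
|---|---|---|
| dies, k_b = 0 | none | {0} |
| dies, k_b = 1 | {1} | {0,1} |
| dies, k_b = 2 | {1,2} | {0,1,2} |
| dies, k_b = 6 | {1,…,6} | {0,…,6} |
| survives | {0,…,6} | {0,…,6} |

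The rows for k_b = 3, 4 and 5 follow the same pattern. Every day-0 record as written belongs to a survivor and has Y = 0. If the survivor range were the slip and should start at 1, a day-0 death would still have no record. So either the rule for deaths must change, or the days must be renumbered for both groups.

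**Step 2: effect on risk and odds ratio under assumed hazards.** The article gives no daily hazards, so these are assumptions: one sign, present from day 0; sign-free daily risk 0.02%; and three hazard-ratio sequences for days 0 to 6. For each group, per infant, let E be the expected records with Y = 1 and N the expected records with Y = 0. Then p = E/(E + N), the implied 7-day risk is 1 − (1 − p)^7, and the odds ratio (OR) is (E/N with sign)/(E/N without sign).

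Worked case, hazard ratios 20, 15, 10, 8, 6, 5, 4:
- Corrected layout, sign: E = 0.013525, N = 6.931471, p = 0.001947, 7-day risk 1.36%. No sign: E = 0.001399, N = 6.994402. OR = 9.75.
- Written layout, sign: E = 0.013525 − 0.004000 = 0.009525, N = 6.921946, p = 0.001374, 7-day risk 0.96%. No sign: E = 0.001199, N = 6.993203. OR = 8.02.
- Share of sign deaths lost: 0.004000/0.013525, about 30%.

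| Hazard ratio, days 0 to 6 | OR corrected | OR as written | 7-day risk with sign, corrected | As written | Fall |
|---|---|---|---|---|---|
| constant 10 | 10.0 | 10.0 | 1.39% | 1.20% | 14% |
| 20, 15, 10, 8, 6, 5, 4 | 9.8 | 8.0 | 1.36% | 0.96% | 29% |
| 40, 15, 8, 5, 4, 3, 3 | 11.2 | 6.4 | 1.56% | 0.76% | 51% |

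With a sign-free daily risk of 0.1% the falls in risk are again about 14%, 29% and 51%.

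**Step 3: what drives the odds ratio.** A second set of assumptions fixes the day-0 share of deaths directly: sign in 5% of windows, 7-day risk 0.4% without and 4% with the sign, remaining deaths spread evenly over days 1 to 6.
- Equal day-0 shares of 10%, 14.3%, 30% or 50% in both groups: deaths kept are 90%, 85.7%, 70% or 50%. Fitted daily risk without the sign is 5.15, 4.91, 4.01 or 2.87 per 10,000, against about 5.7 with the corrected layout. The OR barely moves (about 10.3 against 10.2).
- Unequal shares: 10% without and 30% with the sign give 8.0 against 10.2; 10% and 50% give 5.7 against 10.3.

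The loss of risk follows the overall day-0 share. The loss in the OR needs a larger day-0 share among infants with the sign.

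**The case against.** The strongest reply is that this is a slip of notation. Starting the count at 1 would by itself produce both the number of outcomes and the index range, so their agreement is not independent evidence of a decision. The rest of the text points to the intended layout: day 0 is an admissible death day, survivors start at day 0, and same-day signs are meant to count. The article cannot show that the code follows the literal index. All of this stands as an argument about intent. It does not remove the conflict, because the outcome rule is stated in full and nothing else in the article repairs it.

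Four limits on the point also stand.

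- A reader might infer that day-0 risk is zero by construction. That is true only of the observed day-0 events. Model 2 has one intercept and no day term, so its fitted day-0 probability is that of any other day with the same covariates. Trouble in estimating a day-0 intercept would concern a term the plan does not have.
- A reader might take the lost deaths to be those on the day the sign is seen. The plan does not anchor day 0 at the sign. A sign may first appear on a later day of the window, and a death that same day would be kept.
- The article does not say that a 7-day risk will be derived from model 2. The output it names for the machine learning analysis is adjusted odds ratios, and those need not move.
- The case fatality analysis, the Cox analyses and model 1 do not use this record layout.

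**Conclusion.** Wrong as written. The ranges for deaths and survivors in model 2 cannot both stand with death days 0 to 6. Followed literally, they remove every day-0 death and the day-0 record of every later death. Fitted risk from model 2 is then too low wherever day-0 deaths occur.

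The size cannot be derived from the article. The 14% to 51% falls in implied 7-day risk, and the ORs in the working, rest on assumed hazards with the sign present from day 0. A claim that the sign ORs are necessarily biased would go too far: they are unchanged under a constant hazard ratio and attenuated only when infants with the sign die on day 0 disproportionately. The article does not show a deliberate exclusion of day-0 deaths, and the effect shown is confined to model 2.

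**What to change.** Define k_b + 1 outcomes for each infant who dies: Y_bk for k = 0,…,k_b, with Y_bk = 1 if k = k_b and 0 if k < k_b. Keep k = 0,…,6 for survivors. Renumbering the days 1 to 7 for both groups would be equivalent, provided X_ik uses the same numbering. Before fitting, check that the number of records with Y = 1 equals the number of deaths in the windows.

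The cost is one index in the model definition and the matching line in the data-set code. No new data are needed.

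### As written, Model 2 loses every death on day 0 of the window, and Model 3 is given Model 2's cumulative sign indicator instead of the daily one it announces

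*Protocol article*

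**What the plan says.** Both points are in the protocol article, Machine learning analysis.

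**Model 2.** Its stated purpose is that "we will capture the day in the 7-day window when the death occurred". The death day `k_b` may be any of 0, 1, ..., 6. For an infant who died, "we define $k_{b}$ outcomes", and the index k runs from 1 to `k_b`. That range is printed twice and agrees with the count. The next sentence, opening "For infants that survived, we have", gives survivors a zero outcome on each of days 0 to 6. The sign feature `X_ik` "denotes the presence or absence of sign *i* at any time before or at day k", so it is cumulative.

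**Model 3.** The aim is different: "In our third model, we capture the timing of each clinical sign". To do this, "we consider separate features for the presence/absence of PSBI signs for each day". The equation accordingly has, for each sign, a term for day k and for each of the six days before it, written `X_i^k` to `X_i^(k-6)`. The definition printed under the equation is introduced as defining `X_i^k`, but it is labelled `X_ik` and repeats Model 2's cumulative rule.

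**The concern.** These are explicit coding rules, not details left for later. A programmer who follows them literally builds a Model 2 data set in which deaths on the first day of the window do not exist, although survivors are still counted as at risk on that day. The same programmer builds a Model 3 design matrix whose columns do not mean what the text says.

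Two outputs are at stake. Model 2's predicted risks would be too low, and its ORs might be distorted. Model 3's lag coefficients would be read as the effect of a sign seen a given number of days before, which they would not be. The article says that the ML results in particular may inform changes to the WHO guidance, and possibly an app for community health workers (CHWs).

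**Working it through.** The plan states no figure on this point, so there is none to reproduce. The row rules can be counted exactly. The size of the effect needs assumptions, marked below.

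**Step 1. Model 2 rows and events per infant who died**

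| Death day `k_b` | Rows as written (k = 1..`k_b`) | Events as written | Rows if k = 0..`k_b` | Events |
|---|---|---|---|---|
| 0 | 0 | 0 | 1 | 1 |
| 1 | 1 | 1 | 2 | 1 |
| 2 | 2 | 1 | 3 | 1 |
| 3 | 3 | 1 | 4 | 1 |
| 4 | 4 | 1 | 5 | 1 |
| 5 | 5 | 1 | 6 | 1 |
| 6 | 6 | 1 | 7 | 1 |

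Death days 1 to 6 each keep their event. Only day 0 is lost. Survivors supply a zero at k = 0 and no death can, so the day-0 hazard is 0 by construction.

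**Step 2. Size of the loss.** Let s be the share of window deaths that fall on day 0; the documents do not give it. If deaths are even over seven days, s = 1/7 = 14.3%. When deaths are rare, almost all rows come from survivors, so predicted daily risk is about (1 - s) of what it should be: 6/7, or roughly 14% too low, in the even case.

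**Step 3. Effect on the sign OR.** Take a sign status fixed over the window and rare deaths. Let s1 and s0 be the day-0 shares among deaths with and without the sign. Then, approximately,

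OR as written = OR correct × (1 - s1) / (1 - s0).

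If s1 = s0 the factor is 1. The OR moves only if the timing of death differs by sign status. Two simulations agree. Their assumed inputs are 400,000 infants, 10% with the sign, baseline daily log-odds -6.5 and a sign OR of 10.

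| Assumed timing | Deaths | On day 0 | OR as written | OR with k = 0..`k_b` |
|---|---|---|---|---|
| Constant sign effect | 7,762 | 1,126 (14.5%) | 9.81 | 9.61 |
| Sign effect strongest early | 8,846 | 2,163 (24.5%) | 9.88 | 12.19 |

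**Step 4. Model 3 coefficients.** Assume that the cumulative rule looks back only within the seven-day window. A sign seen once, l days before day k, then switches on the columns for lags 0 to l. If c_l is the coefficient of cumulative column l and b_l is the effect of a sign seen l days before, then b_l = c_0 + ... + c_l, so c_l = b_l - b_(l-1). Each coefficient after the first is a difference between neighbouring lags.

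The table uses assumed b. The simulated fits have 600,000 rows, intercept -5 and the sign drawn independently each day with probability 0.1.

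| Lag (days) | 0 | 1 | 2 | 3 | 4 | 5 | 6 |
|---|---|---|---|---|---|---|---|
| Assumed daily log-OR | 2 | 1.5 | 1 | 0.5 | 0.25 | 0 | 0 |
| Fit, daily coding | 2.02 | 1.49 | 1.06 | 0.48 | 0.22 | 0.06 | 0.01 |
| Algebra, one sighting, cumulative | 2 | -0.5 | -0.5 | -0.5 | -0.25 | -0.25 | 0 |
| Fit, cumulative coding | 2.00 | -0.09 | -0.12 | -0.44 | -0.15 | -0.12 | -0.05 |

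Read singly, the cumulative row would suggest that a sign seen one to four days earlier adds no risk or protects. By assumption it raises risk. Over seven days, 2^7 = 128 daily patterns per sign collapse to 8: no sign, or one of seven first-onset days.

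**Step 5. How often this bites.** Table 1 schedules visits on days 0, 2, 6, 13, 20, 27, 34, 41, 48 and 59. A seven-day window holds more than one scheduled visit only if it ends on days 2 to 8; for example, days 0 to 6 hold three. Windows ending later hold at most one.

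**The case against.** **Model 3 is a copying slip and the intent is clear.** The prose and the lagged equation all point to daily features, and the faulty line uses a symbol that the equation does not contain. This is probably right. It explains the error, but no other text corrects it.

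**Cumulative coding often does little harm.** With one sighting per window, the two codings are an invertible recoding of each other. Unpenalised fit is identical, and lag effects come back as running sums. This stands for windows ending after day 8. It does not cover penalised fits, and Elastic Net is one of the planned methods: a penalty on the c_l pulls neighbouring lags together, not each effect towards zero. Nor does it cover coefficients read one at a time, or early windows with several visits. The article names fast breathing in the first week as a possible starting point for the app, so early windows matter.

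**A reader might infer that the lost deaths are those on the day a sign is found, and so the most informative ones.** The documents do not support this. They never tie day 0 of the window to the day of a sign, and `X_ik` can switch on at any day in it.

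**A reader might also infer a large fixed bias.** With an assumed hazard falling as 4:2:1:0.6:0.5:0.4:0.3 in the sign group only, 46% of that group's deaths fall on day 0 and the OR drops from 12.87 to 8.09. That shape has no source in the documents. With constant hazards the ORs are 10.05 (correct rows) and 10.07 (as written). With the same falling shape in both groups they are 10.22 and 10.11.

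**The single intercept in Model 2 is not an error.** A constant baseline daily risk is a legitimate simpler model. This stands.

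**Conclusion.** Both definitions are wrong as printed and should be corrected before the data sets are coded. Model 2 admits death on day 0 and then gives such a death no row. That follows from the text alone and needs no assumption. The share lost is unknown: about 1 in 7 under an even spread, more or less otherwise, with predicted risk too low in about that proportion. Bias in the sign ORs is conditional on death timing differing by sign status and may be negligible.

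Model 3's printed feature contradicts its own announced purpose. If it is coded literally, the lag coefficients are contrasts and not effects of a sign on a given day. Cumulative columns still carry the day of first onset, so some timing information survives; recurrence and persistence do not.

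It would go too far to say that neither model estimates anything useful, or that the trouble reaches the study's other analyses. Model 1, the case-fatality analysis, the Cox regression and the regularised Cox model do not use these definitions.

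**What to change.** - **Model 2:** give each death outcomes for k = 0, ..., `k_b` (that is, `k_b` + 1 rows), so that the index matches the survivors' 0 to 6. Correct the count and both printed ranges.
- **Model 3:** define `X_i^k` = 1 if sign i is present on day k, and use that symbol throughout. Correct the stray subscript b in the second line of the equation.
- **Unassessed days:** in Model 3, distinguish a day with no CHW assessment from a day assessed with the sign absent. Otherwise daily coding would record every day between visits as sign-free. It would do the same for hospital days, when the Analysis section says CHWs did not visit (4% of ANISA and 5% of AFRINEST infants were hospitalised). The one-hot encoding already planned for Model 3 can carry a third, not-assessed level.
- **Optional:** day-specific intercepts in Model 2 would let baseline risk vary over the window. This is an improvement, not a repair.

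The cost is a few lines in the plan and in the data-set code. No new data are needed.

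### Model 3 is meant to use a separate feature for each sign on each day, but its printed definition repeats model 2's cumulative rule, so coefficients at lags 1 to 6 would be contrasts between neighbouring lags

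*Protocol article*

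**What the plan says.** All of this is in the protocol article, section Machine learning analysis.

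- The opening paragraph sets the general approach: "Presence/absence of PSBI signs at different times will be treated as separate features". Risk of death on a day is predicted from the signs on that day and the six days before it.
- Model 2 is cumulative by design. Its feature X_ik "denotes the presence or absence of sign *i* at any time before or at day k".
- Model 3 is introduced as the step beyond that: "In our third model, we capture the timing of each clinical sign", and then "To achieve this, we consider separate features for the presence/absence of PSBI signs for each day". Its equation gives each sign seven coefficients, with superscripts 0 to −6, on features written with a day superscript (k, k−1, ..., k−6).
- The definition printed under the model 3 equation is the same display as for model 2: 1 if the sign is present on day k or on any earlier day, otherwise 0. Its left-hand side is model 2's symbol X_ik, although the line leading into it speaks of X with superscript k, for k = 0 to 6.
- The section on model 3 closes with "In the case of model 3, 1-hot encoding will be used to construct matrix X containing all input features".

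**The concern.** The prose and the equation describe one indicator per sign per day. The definition describes a running indicator that stays at 1 once the sign has appeared. These are different design matrices, and the definition is the line an analyst would turn into code.

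Under the running rule the seven features for one sign are nested. A sign first seen L days ago sets the features at lags 0 to L to 1. The features then depend only on the earliest day the sign was present, and the coefficient at lag 3, say, no longer describes a sign found three days ago.

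What is at stake is how the timing results are read. The article says that results, the machine learning results in particular, will be considered for changes to the IMCI guidance for young infants and perhaps for an app for community health workers. If the lag coefficients were exponentiated and read as day-specific odds ratios, the importance of signs found on earlier days could be misjudged.

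**Working it through.** The article gives no figure for this point, so there is none to reproduce. The check is algebra, followed by a simulation on assumed values.

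**1. Notation.** Let γ(l) be the true log odds ratio of death for a sign seen only at lag l, for l = 0 to 6. Let C(l) be the printed feature at lag l: 1 if the sign was present at lag l or earlier. Let β(l) be its coefficient.

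**2. Identity for a single sign-day, no penalty.** A sign seen only at lag l sets C(0), ..., C(l) to 1 and leaves the rest at 0. Its contribution to the log odds is β(0) + ... + β(l), which must equal γ(l). Hence

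- β(0) = γ(0), so exp β(0) is the full odds ratio at lag 0;
- β(l) = γ(l) − γ(l−1) for l = 1 to 6, so exp β(l) = OR(l) / OR(l−1).

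**3. Numbers.** The true odds ratios below are assumptions chosen to show the range.

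| Assumed pattern | True ORs, lags 0 to 6 | exp β under the printed rule, lags 0 to 6 |
|---|---|---|
| Fading | 8, 6, 5, 4, 3, 2.5, 2 | 8.00, 0.75, 0.83, 0.80, 0.75, 0.83, 0.80 |
| Constant | 4 throughout | 4.00, then 1.00 six times |
| Rising | 2, 2.5, 3, 4, 5, 6, 8 | 2.00, 1.25, 1.20, 1.33, 1.25, 1.20, 1.33 |
| Humped | 3, 5, 8, 6, 4, 3, 2 | 3.00, 1.67, 1.60, 0.75, 0.67, 0.75, 0.67 |

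For example, in the fading row lag 1 is 6/8 = 0.75 and lag 2 is 5/6 = 0.83. In none of the four patterns does a value at lags 1 to 6 equal the true odds ratio at that lag.

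**4. Simulation.** Unpenalised logistic fits used 500,000 windows per pattern, an assumed intercept of −4, and one sign-day in half of the windows. For the fading pattern, features defined by the day alone returned 7.71, 6.16, 4.99, 3.97, 2.98, 2.53, 2.02, close to the assumed values. The cumulative features returned 7.71, 0.80, 0.81, 0.80, 0.75, 0.85, 0.80. Across all four patterns the cumulative fits agreed with the algebra to within about 0.06 at lags 1 to 6.

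**5. Recurring signs.** With the sign present independently on 10% of days, the cumulative fit to the fading pattern gave 8.11, 1.05, 1.08, 0.98, 0.96, 0.93, 0.92. The past lags sit near 1, some above and some below, although the true values run from 6 down to 2.

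**6. Which case is usual here.** Table 1 of the article schedules home visits on days 0, 2, 6, 13, 20, 27, 34, 41, 48 and 59. A 7-day window ending on day 9 or later holds at most one scheduled visit. Windows ending on days 2 to 8 hold two or three. On the schedule, the single sign-day of step 2 is therefore the usual case after the first days of life.

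**7. Penalty.** Elastic Net, one of the methods named for these models, pulls each β towards 0. With day-specific features that shrinks each lag's effect towards no effect. With the printed features it shrinks differences between neighbouring lags, that is, it pulls the lags towards one common effect. Fit and feature selection would differ accordingly.

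**The case against.** The strongest reply is that this is a copying slip. The definition repeats model 2's display under model 2's symbol, and the model 3 equation has another slip, pairing a coefficient for sign 2 with a feature subscripted b. The opening paragraph, the sentence introducing model 3 and the 1-hot sentence all point to per-day features, and an analyst following the prose would probably code them so. That is likely right. It makes the correction cheap, but it does not make the printed rule harmless if it is coded.

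Several further points stand and limit the concern:

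- A reader might infer that any harmful past sign would get an odds ratio below 1. The documents do not support that. It needs harm that fades with lag, and the article gives no lag-specific effects; constant harm gives 1 and rising harm gives values above 1.
- A reader might also infer that model 3 could not carry timing at all. For a single sign-day the printed coding is an exact reparametrisation: running sums of the coefficients recover each lag's log odds ratio, and unpenalised predictions are unchanged.
- The formula for the odds ratio as exp(β) is written beside model 1. No lag-specific odds ratio is explicitly promised for model 3, and the formula would not apply to XGBoost, which is also listed.
- Losing the distinction between a sign that cleared and one that persisted matters little when most windows hold one scheduled visit.
- The index range 0 to 6, which leaves day k−6 undefined when k is below 6, is a matter of notation, since the opening paragraph states the intended window.

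The case-fatality analysis, the Cox analyses and models 1 and 2 do not use this definition.

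**Conclusion.** The contradiction is real and should be corrected before model 3 is coded. The stated purpose is a separate feature for each day, and the only definition given is cumulative. If the definition is followed, exp(β) at lags 1 to 6 is not the odds ratio of a sign found that many days ago, while lag 0 keeps its meaning.

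The size depends on effects that the article does not give. Under the assumed fading pattern, true past-lag odds ratios of 6 down to 2 would appear as 0.75 to 0.83. Under a constant odds ratio of 4 they would all appear as 1.00, as if earlier signs added nothing. The identity is exact for one sign-day per window without a penalty; recurring signs blur it and Elastic Net changes the values. The harm is to the interpretation of timing and to what the penalty acts on. It is not a demonstrated failure of prediction.

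**What to change.** For model 3, replace the printed definition with: X_i^d = 1 if sign i was recorded on day d itself, and 0 otherwise, for d = k−6, ..., k, with d counted in days of age. Use this one notation in the equation, in the line that introduces the features and in the definition, and correct the stray subscript b.

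Most days have no scheduled visit, so a 0 would otherwise mix days not assessed with days assessed without the sign. State how the two are told apart, for example with a visit indicator for each day. The same indicator covers lags that fall before birth in infants younger than six days.

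The cost is one definition, a sentence on unassessed days and the matching feature code. No new data are needed.
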